### Participant timeline {13}

Participant timeline is summarised in SPIRIT (Fig. 2).

**Fig. 2 Fig2:**
[figure not shown]
Spirit study schedule of enrolment, interventions and assessments

### Sample size {14}

The sample size in this prospective study was calculated according to a similar study with the mean lowest SpO_2_ 95.2% (LFNC) and 99.3% (HFNC), with a standard deviation of 0.1 respectively in two different oxygen therapies [28]. Please note that this sample size is, although based on a similar study which compared the HFNC vs LFNC [8], also based on a different indication and with use of shorter (< 75 min) duration of treatment. To achieve 80% statistical power with α error rate of 0.05, the number of patients was calculated to be 94 for each group. An online statistical calculator, Statulator, was used to calculate the sample size for comparing two independent means.

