In a number of indications, PSA is applied for longer periods. One of these indications is radiofrequency catheter ablation (RFCA) in AF patients with a duration a PSA of more than 3 h. AF ablation has become one of the most common procedures in the electrophysiology lab with rapidly increasing volumes. A recent survey by the European Heart Rhythm Association (EHRA) shows that in 2019, 32% of all procedures are performed under conscious sedation and 27.5% of all procedures under deep sedation [10]. The most commonly used hypnotic drugs were propofol and midazolam, whereas the most commonly used opioids were remifentanil and fentanyl [10]. The potential positive effects of HFNC in this growing patient population is unclear.

In the Maastricht University Centre patients undergoing RFCA are managed by deep sedation with a combination of low dose remifentanil and propofol, as patient movement may result in shifts of the electro-anatomical maps required for the navigation of the ablation catheter and might cause serious complications including air embolisms and cardiac tamponade. Deep sedation is associated with an increased incidence of upper airway collapsibility and disturbed central respiratory drive [13], which results in forced breathing movements during obstructive respiratory events resulting in pronounced intrathoracic pressure swings leading to electro-anatomical map shifts. Additionally, if LFNC is used (standard of care) a sudden drop of oxygen saturation (SpO_2_ < 90%) occurs in 1.5% of patients [17]. Increased pressure in the upper airway during HFNC might reduce upper airway collapsibility during sedation [21] and facilitates active gas exchange during times of hypoventilation [12] allowing stable and long PSA procedures. Additionally, HFNC may enhance carbon dioxide clearance by an entrained and highly turbulent supra-glottic flow vortices created by high-flow nasal oxygen and cardiogenic oscillations [12]**.**

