### Interim analyses {21b}

After inclusion of 50 participants in each group we will perform a blinded sample size control with the SpO_2_ data of the participants. The sample size is based on a similar study which compared the HFNC vs LFNC [8]. However, this study was based on a different indication and conscious sedation instead of prolonged deep sedation.

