## Discussion

Procedural sedation and analgesia has become a common practice given the increasing demand to relieve anxiety, discomfort and pain during invasive diagnostic and therapeutic procedures. In 2018, the Department of Anaesthesiology at MUMC+ performed 2040 PSA procedures. The majority (*n* = 888) of PSA procedures were performed during RFCA and cardiac electrophysiology testing. Our experience is that as the procedure and PSA time increases saturation more often shows a gradual decrease and desaturations occur more frequent. The aim is to prevent patients for desaturations and hypoxemia. BMI as selection criteria was therefore decreased to 32 kg m^−2^ instead of 35 kg m^−2^. And the PSA (and procedure) time is limited to a maximum of 4 h.

To our knowledge, this is the first study to investigate the effects of HFNC during prolonged deep sedation in patients undergoing RFCA. HFNC is increasingly used as a technique for oxygen delivery in procedural sedation and analgesia The effect of HFNC vs LFNC during sedation has been investigated in several small studies. No difference in primary outcomes of oxygen desaturation was reported. The explanation could be the small sample-sizes and the level of sedation. The intervention could have a positive effect in this study because deep sedation is performed in supine position for a prolonged time up to 4 h.

The sample size in this prospective study was calculated and adjusted using a similar study which compared HFNC vs LFNC in a different population [26]. In this study, participants underwent dental surgery. However, the duration of sedation and treatment were shorter (< 75 min), which will affect primary outcome [26]. Therefore, we decided to perform a sample size control.

The secondary outcomes include ratings of experiences of participants and staff using 5 point Likert scales. Validated questionnaires were preferred, but unfortunately these are not available.

To ensure that all colleagues work according to the study protocol and follow GCP guidelines, education and training is provided. The AC are trained to obtain informed consent. The AC are instructed and trained in the use of the Optiflow and Vsign. They are also trained to provide PSA according to this study protocol during sedation. The group of PAs and AC exists of 7 colleagues.

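### The stated inputs (95.2% vs 99.3%, SD 0.1) do not give 94 per group; 94 needs an SD of 10 points, which cannot hold at a mean of 99.3%, so the 80% power figure is wrong

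*Protocol article*

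**What the plan says.** Under Sample size {14} the article takes as planning values "the mean lowest SpO_2_ 95.2% (LFNC) and 99.3% (HFNC), with a standard deviation of 0.1 respectively in two different oxygen therapies". No unit is given for the SD, and the means beside it are in percent. It continues "To achieve 80% statistical power with α error rate of 0.05" and reports that "the number of patients was calculated to be 94 for each group", using an online calculator for two independent means. Trial design {8} carries this forward as 188 participants, allocated 1:1. The primary analysis is an independent-samples t-test on lowest SpO2.

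The source of these figures is given in several ways. Sample size {14} cites [28] for the means and SD, and in the next sentence cites [8]. Interim analyses {21b} says "The sample size is based on a similar study which compared the HFNC vs LFNC [8", that is reference 8. The Discussion says the size was "calculated and adjusted using a similar study which compared HFNC vs LFNC in a different population [26", that is reference 26.

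Interim analyses {21b} also plans a blinded sample size check after 50 participants per group. It states no decision rule.

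**The concern.** A 4.1-point difference with an SD of 0.1 point is a standardised difference of 41. No trial needs 94 patients per group to detect that, so either the SD or the number of patients is not what the text says.

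If the inputs and the result do not belong together, the 80% power claim has no basis, and it is the only justification given for 188 patients. The Abstract and the Background both motivate the trial by a lack of adequately powered studies. The blinded check in {21b} is there because the source study fits poorly, so it needs a usable target difference and SD to be compared with.

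**Working it through.** **Inputs** (Sample size {14}; Trial design {8}): difference 99.3 − 95.2 = 4.1 points; SD 0.1, no unit; power 80%; alpha 0.05, sidedness not stated and taken as two-sided; allocation 1:1; stated n = 94 per group. 188 = 2 × 94, so no dropout allowance is included.

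**Formula:** n per group = 2 × (1.960 + 0.842)² × (SD/4.1)², where (1.960 + 0.842)² ≈ 7.849.

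**Reproducing 94**
- SD 0.1 point, same unit as the means: n = 0.009. That is 1 per group by formula, and 2 as a practical minimum. Power at 94 per group is about 100%.
- SD 10 points (means 0.952 and 0.993, SD 0.1 as fractions): n = 2 × 7.849 × (10/4.1)² = 93.4, rounded up to 94. The t-based solution is 94.4.
- One-sided alpha with SD 10 gives 74, so 94 corresponds to a two-sided test.
- Variants that keep SD 0.1 in percentage points (one-sided alpha, 90% power, dropout of 5–20%, or 0.1 read as a standard error from an assumed 10–30 patients) all stay at 1 or 2 per group.
- Treated as two proportions, 0.952 vs 0.993 gives 246, so 94 does not come from there.

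The stated size therefore implies an SD of 10 points.

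**Is an SD of 10 possible?** A variable on 0–100 with mean m has SD at most √(m(100 − m)).
- HFNC: √(99.3 × 0.7) = 8.34. An SD of 10 is impossible.
- LFNC: √(95.2 × 4.8) = 21.4. An SD of 10 is possible.
- Unequal SDs: for an average variance of 100, the LFNC variance must be at least 200 − 69.5 = 130.5 (SD 11.4) even with HFNC at its ceiling. That ceiling is reached only if every HFNC value is 0 or 100.

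**Power at 94 per group for 4.1 points** (normal approximation; common SDs are assumptions)

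| Common SD (points) | n per group needed | Power at 94 |
|---|---|---|
| 3 | 9 | >99.9% |
| 5 | 24 | >99.9% |
| 8 | 60 | 94.0% |
| 8.34 (HFNC ceiling) | 65 | 92.1% |
| 10 (not feasible) | 94 | 80.3% |

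**What the article itself suggests about the SD.** It gives three rates below 90%. If lowest SpO2 were roughly normal around 95.2, then SD = (95.2 − 90)/z:
- 1.5% in the Background ("a sudden drop of oxygen saturation (SpO_2_ < 90%) occurs in 1.5% of patients [17", reference 17): 5.2/2.170 = 2.4.
- 168 per 1000 in general procedural sedation: 5.2/0.962 = 5.4.
- 10 of 30 on standard oxygen at bronchoscopy: 5.2/0.431 = 12.

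These are illustrative. They join rates from different populations to a mean from yet another study and assume normality for a bounded minimum.

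**Difference detectable at 94 per group with 80% power** (t-based, 0.411 × SD): 0.8 points at SD 2, 1.2 at SD 3, 2.1 at SD 5, 3.3 at SD 8.

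**Sources side by side.** The Background places [28] after major surgery, [8] in acute respiratory failure and [26] in dental surgery. {21b} describes its source, [8], as a conscious-sedation study, which does not match the Background's description of [8].

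**The case against.** The best defence is that 94 is not arbitrary. It follows exactly if 0.1 is meant as a fraction, so the calculator was used properly and only the printing is at fault. This explains where 94 came from, but it does not rescue the statement, because the resulting common SD of 10 exceeds what a mean of 99.3% allows.

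It is also fair that SD 10 is possible for LFNC alone. With an LFNC SD of 12 and an HFNC SD of 5, the average variance is (144 + 25)/2 = 84.5 and n = 2 × 7.849 × 84.5/16.81 ≈ 79, still below 94.

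Four stronger readings are tempting and are not supported:
- **That the trial is underpowered.** For the stated 4.1 points the error runs the other way. For the real effect the documents do not say.
- **That the SD is really about 2.4, so differences near 1 point will reach significance.** That uses only the 1.5% rate and ignores 16.8% and 10 of 30.
- **That an SD of 10 contradicts the article's own desaturation rate.** It would put about 30% of LFNC patients below 90% under normality, but the article's rates run from 1.5% to 33%.
- **That the blinded check would stop the trial at 100 patients.** For 4.1 points, an SD below about 7.3 would return fewer than 50 per group, but {21b} contains no stopping or reduction rule. A check on observed SpO2 data would ordinarily replace the planning SD, and its detail may sit in the full protocol or SAP.

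The conflict of citations is editorial, and a numbering slip cannot be excluded because the reference list is not shown. It still leaves the origin of the means and SD unidentified.

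**Conclusion.** The point stands. As printed, the inputs give 1 or 2 per group, not 94. The size of 94 rests on an SD of 10 points, which is impossible as a common SD or for the HFNC arm at the stated mean. At any feasible common SD, power for 4.1 points is about 92% or more, so the stated 80% is wrong and the trial is oversized for its own target.

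This rests on a two-sided test, the stated means, a 0–100 scale and a common SD. The unequal-SD exception needs an unrealistic HFNC distribution. The validity of the t-test is not affected. What 94 per group can detect in this population remains open, because neither the SD nor the effect is known. No other section of the article corrects the calculation.

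**What to change.** In Sample size {14}:
- Give means and SD in the same unit, from one identified source.
- Withdraw the claim of 80% power for 4.1 points.
- Keep the planned 188 and report the difference detectable with 80% power over a plausible range of SDs (for example 0.8 points at SD 2, 2.1 at SD 5, 3.3 at SD 8), beside the difference the investigators regard as clinically relevant.

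Make Sample size {14}, Interim analyses {21b} and the Discussion cite the same study and describe it consistently. In {21b}, say that the blinded check uses the observed pooled SD with the restated target difference, not the SD of 0.1.

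The cost of the rewrite is wording only, with a less tidy power statement. The rewrite itself adds no patients. Whether the blinded check later calls for a different number depends on the observed SD and the restated target.

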### Recruitment {15}

The patient will be informed by the cardiologist about the indication for a RFCA treatment during an outpatient clinic visit at the cardiology department. The patient is also informed that treatment will be under deep sedation or general anaesthesia. During this consultation, the patient is asked whether he/she may be approached about current studies. Each patient who indicates to be open to participate in current studies will receive a patient information letter and will be informed by phone about the study aims and risks.

### Assignment of interventions: allocation

#### Sequence generation {16a}

The allocation of participants to groups will be randomised using computer-randomised allocations (data management system used: Castor). Sequence generation will be performed in blocks of 2,4,6 stratified by gender.

#### Concealment mechanism {16b}

Allocation concealment will be guaranteed with sealed opaque envelopes.

#### Implementation {16c}

The allocation sequence will be generated by 2 members of the research team. After screening for eligibility, the patients can be allocated. The patients will be allocated on the day of treatment. The assigned allocation by the enrolling will be communicated to the physician assistant (PA)/nurse anaesthetist (NA) using sealed envelopes. The PA/NA performs the treatment which is assigned to the participant.

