### Trial design {8}

This study is a single centre, randomised controlled trial and is designed to evaluate the superiority of HFNC compared with LFNC. Based on a power-calculation {14}, it is aimed to include 188 participants. The allocation ratio is 1:1. Patients will be randomised to the intervention group (HFNC during deep sedation) or the control group (LFNC during deep sedation). Figure 1 summarises the study design.

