### Oversight and monitoring

#### Composition of the coordinating centre and trial steering committee {5d}

All researchers will be a part of the trial management committee. Study coordination will be performed by the Department of Anaesthesiology MUMC+. Data acquisition will be performed by 2 members of the research team. Statistical analysis will be performed by the independent statistician

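### The protocol does not say whether Castor or team-held envelopes control allocation, and does not separate the sequence generators from enrolment in a single-centre trial without bedside blinding

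*Protocol article*

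**What the plan says.** All references are to the protocol article.

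- **Design.** Trial design {8}: "This study is a single centre, randomised controlled trial and is designed to evaluate the superiority of HFNC compared with LFNC". It continues: "The allocation ratio is 1:1". The planned total is 188.
- **Sequence.** Sequence generation {16a} names Castor as the system for computer-randomised allocation and adds: "Sequence generation will be performed in blocks of 2,4,6 stratified by gender".
- **Concealment.** Concealment mechanism {16b}: "Allocation concealment will be guaranteed with sealed opaque envelopes".
- **Who does it.** Implementation {16c}: "The allocation sequence will be generated by 2 members of the research team". Patients are allocated on the treatment day, after eligibility screening, and the result reaches the physician assistant or nurse anaesthetist in a sealed envelope.
- **Blinding.** Who will be blinded {17a} and Procedure for unblinding {17b}: only the data analysts are blinded.
- **Staff.** The consent section {26a} has a physician assistant take consent at the outpatient clinic. The Discussion says that the group it calls AC is trained both to obtain consent and to give the sedation, and that "The group of PAs and AC exists of 7 colleagues".
- **Data.** Composition of the coordinating centre {5d}: "Data acquisition will be performed by 2 members of the research team". The same section assigns the statistical analysis to an independent statistician.

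**The concern.** Sections {16a}, {16b} and {16c} can be read in two ways. In one, Castor holds the sequence and releases one result at a time, with the envelope only carrying that result to the bedside. In the other, two team members produce a list, fill envelopes from it, and the envelopes are the concealment. The two readings protect the sequence very differently, and the text does not choose between them.

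The setting makes the choice matter. There is one centre, the treating staff see the device in use, the staff group is small and partly overlaps with those taking consent, and the block sizes are in print. The article is dated 9 May 2022, and its Trial status section plans recruitment up to 31 August 2023, so the sizes were public while patients could still be enrolled.

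If someone involved in enrolment can anticipate the next arm, a late exclusion or a change in patient order can depend on it. The exclusion criteria are worded as grounds on which patients can be excluded, and they include judgement items such as an expected difficult airway. The primary outcome is a single extreme value, the lowest SpO2, which plausibly depends on airway difficulty. Airway difficulty is not among the covariates in {20a}, so the adjusted analysis would not remove such an imbalance. The statement in {17a} that outcomes are objective answers measurement bias, not selection bias.

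**Working it through.** The protocol gives no predictability figure to reproduce, so the check asks how well the next allocation can be guessed.

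**Inputs.** Ratio 1:1 ({8}). Block sizes 2, 4 and 6, stratified by gender ({16a}). *Assumptions, because the article is silent:* each block size has probability 1/3; the guesser knows every earlier allocation in the stratum, in order; list length is 94 per stratum (188/2, for illustration, as the gender split is not given).

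**Step 1. One block of size 2m.** The guesser picks the arm with fewer allocations so far and tosses a coin when they are level. The expected number correct is m + 2^(2m−1)/C(2m, m) − 1/2. The expected number of allocations fully determined, if the block boundaries are known, is 2m/(m + 1).

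| Block | Correct guesses | Rate | Determined | Rate |
|---|---|---|---|---|
| 2 | 1 + 2/2 − 0.5 = 1.5 | 75.0% | 1 | 50.0% |
| 4 | 2 + 8/6 − 0.5 = 2.833 | 70.8% | 1.333 | 33.3% |
| 6 | 3 + 32/20 − 0.5 = 4.1 | 68.3% | 1.5 | 25.0% |

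Exact enumeration of all sequences gave the same rates.

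**Step 2. Equal mix of 2, 4 and 6, boundaries known.**

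- Correct: (1.5 + 2.833 + 4.1)/(2 + 4 + 6) = 8.433/12 = 70.3%.
- Determined: (1 + 1.333 + 1.5)/12 = 3.833/12 = 31.9%.

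**Step 3. Boundaries hidden.** In 2,000 simulated lists of 94, each allocation was guessed from the exact posterior over block size and position.

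| Sizes | Guessed correctly | Known with certainty |
|---|---|---|
| 2, 4, 6 | 70.1% | 4.2% |
| 4, 6 | 69.2% | 5.4% |
| 4, 6, 8 | 67.9% | 2.3% |

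Simply guessing the arm that lags within the stratum gave the same rates of correct guesses. Every block ends balanced, so the running difference in the stratum equals the difference within the current block. Hiding the boundaries therefore takes away certainty (31.9% falls to 4.2%) but hardly changes the guess rate.

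**Step 4. What the block size contributes.** Moving from 2, 4, 6 to 4, 6, 8 lowers the guess rate by 70.1 − 67.9 = 2.2 points. Moving to 4, 6 lowers it by 70.1 − 69.2 = 0.9 points and raises certainty from 4.2% to 5.4%. Who generates, holds and releases the sequence is not captured by any of these figures, and that is where most of the protection lies.

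**The case against.** Sealed opaque envelopes with varying block sizes are an accepted method, and an article need not describe envelope numbering or custody. That stands, and the absence of those details is not held against the plan. Team members may also have set up the sequence inside Castor, with envelopes only passing on each result. That reading fits the text, but the text does not say so.

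Several stronger readings are tempting and are not supported:

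- *The two generators know every allocation.* The article mentions no printed list and does not say that the generators enrol patients.
- *The same two people acquire the data.* {5d} also speaks of two team members but does not say that they are the same two. Data collection after allocation is in any case not a concealment matter.
- *All seven staff see every earlier allocation.* The Discussion gives only the size of the group. Open label does not mean that each member tracks colleagues' patients by gender.
- *Nothing is blinded.* The data analysts are.
- *Eligibility is judged on the treatment day.* {16c} places allocation on that day, after screening, and {26a} places preoperative screening and consent at the outpatient clinic. Late exclusion or reordering remains possible, but no section describes it.

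The 50% benchmark is also strict, since every permuted-block design exceeds it. Consent before allocation and opaque envelopes reduce the risk but do not remove it.

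**Conclusion.** The point holds as an unresolved mechanism and an open risk. The article names two routes to allocation without saying which controls it, and it does not separate the sequence generators from enrolment, in a setting where foreknowledge could be used. A guess rate of about 70% is an upper end: it rests on complete, ordered knowledge of earlier allocations in the stratum and on equally likely block sizes. It measures predictability and does not estimate bias in the treatment effect. With hidden boundaries about 4% of allocations are certain, so for treating staff the risk is guessing rather than knowing. The published block of 2 adds little. The change is worth making because better concealment is available in a system the trial already uses, and selection bias, once present, cannot be reliably repaired in analysis.

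**What to change.** Amend {16a} to {16c} so that they describe one mechanism:

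1. Castor releases each allocation live, on the treatment day, only after consent and eligibility have been irreversibly recorded for that patient. Envelopes are no longer used.
2. The sequence is configured by someone who does not enrol, treat, collect data or analyse. This should not be the trial statistician in {5d}: that person performs the analysis, and {17a} keeps the analysts blinded.
3. Block sizes for the remaining patients are kept from enrolling and treating staff.

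The cost is a Castor configuration change and a protocol amendment, notified as {25} provides. No extra patients are needed. If recruitment has begun, the change applies to the remaining patients. The Trial status section gives conflicting start dates, so how many remain cannot be told from the article. Abandoning an open block at the switch leaves an imbalance of at most 6/2 = 3 patients in each gender stratum, or 6 over two strata, which is negligible against 188.
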